### (3) Type I error control for interim efficacy analysis based on OS

One interim analysis for OS is planned for this trial after 70% of the planned OS events (348 cases). If expected efficacy is observed, early declaration of the trial due to efficacy would be considered. The interim analysis will be conducted by iDMC.

Type I error will be controlled by the O'Brien-Fleming spending function approach. According to the O'Brien-Fleming spending function approach, in the interim efficacy analysis based on OS, the one-side significance level is set as  $\alpha_1 = 0.0074$  in the interim analysis and  $\alpha_2 = 0.0228$  in the final analysis.

- In the interim analysis:  $P_1 \leq \alpha_1$ , early declaration of the trial will be considered according to actual results;
- In the final analysis:  $P_2 \leq \alpha_2$ , the between-group difference in OS will be considered statistically significant.

$P_1$  = the one-side P value in the interim analysis;  $P_2$  = the one-side P value in the final analysis;

The tests sequence and type I error in the final analysis are shown in the following figure:

[figure not shown]

A two-sided test with a significance level of  $\alpha=0.05$  will be used for secondary efficacy endpoints and safety analysis. Two-sided  $P \leq 0.05$  will be considered statistically significant with a 95%CI.

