### **Secondary objectives:**

- To compare the ORR, DCR, duration of response (DOR), 6-month PFS rate, 12-month PFS rate, 12-month OS rate, 18-month OS rate, and quality of life (QOL) across the three treatment arms.
- To compare safety and tolerability based on incidence and severity of AEs and serious adverse events (SAEs), as well as abnormal laboratory test indicators across the three treatment arms.
- To evaluate the immunogenicity of TQB2450 plus anlotinib and EC.

- To explore additional biomarkers related to efficacy, mechanisms of action, safety, and/or pathological mechanisms.

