#### Secondary endpoints:

- ✓ PFS per RECIST version 1.1 and iRECIST, ORR, DCR, DOR, 6-month PFS rate, 12-month PFS rate, 12-month OS rate, 18-month OS rate, and QOL assessed by investigators.
- ✓ Safety and tolerability based on incidence and severity of AEs and SAEs, as well as abnormal laboratory test indicators.

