## 11. QoL

The QoL will be evaluated from various aspects through questionnaires. The exploratory objective of this trial is to evaluate the HRQOL, aiming to collect information on drug application as early as possible. The questionnaires for HRQOL will be completed at the scheduled time point.

To avoid being influenced by the investigator(s) or new conditions, the questionnaire should be

completed before any clinical examination and evaluation, as well as any new disease information and new treatment. The questionnaire will be stored as source documents.

Investigator(s) will review the questionnaire and evaluate the clinical signs. Any unobserved AEs in clinical evaluation will be recorded in the CRF.

The EuroQol five-dimensional (EQ-5D) descriptive system consists of a questionnaire and utility value conversion table. The questionnaire is reported for health conditions and EQ visual analog scale (EQ-VAS) score, while the utility value conversion table is reported for EQ-5D index values.

The questionnaire contains EQ-5D health state classifications and EQ-VAS. EQ-5D health state classification contains 5 dimensions, including mobility, self-care, usual activities, pain discomfort, and anxiety/depression. Each dimension contains 3 levels, including no problems, some problems, and extreme problems. EQ-VAS is a 20 cm vertical visual analog scale. 100 at the top indicates the best health you can imagine and 0 at the bottom indicates the worst imaginable health state.

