### 13.2.2 Size of a Test

#### (1) Type I error control in the multiple-group comparison

There are 3 arms in this trial:

Intervention arm 1: TQB2450, Anlotinib, Carboplatin, and Etoposide

Intervention arm 2: TQB2450 placebo, Anlotinib, Carboplatin, and Etoposide

Control arm: TQB2450 placebo, Anlotinib placebo, Carboplatin, and Etoposide

The primary efficacy endpoints of this trial are PFS and OS. In this trial, a fixed-sequence test will be used for comparisons between treatment groups:

- a) The PFS between intervention arm 1 and the control arm (PFS1) will be first tested with the two-sided significance level of 0.05 (one-side, 0.025). If PFS1 is statistically significant, the OS between intervention arm 1 and the control arm (OS1) will be then tested.
- b) If OS1 is statistically significant, the PFS between intervention arm 2 and the control arm (PFS2) will be tested.
- c) If PFS2 is statistically significant, the OS between intervention arm 1 and intervention arm 2 (OS3) will be then tested.
- d) If OS3 is statistically significant, the OS between intervention arm 2 and the control arm (OS2) will be tested.

The overall significance level is set as 0.05 at two-side (one-side, 0.025). Familywise error rate (FWER) will be controlled by the fixed order test when each hypothesis presupposes the rejection of all previous tests.

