#### **13.4.2 Analysis of Secondary Efficacy Endpoints**

##### **➤ ORR**

The number and percentage of subjects with an objective response (PR or CR) will be presented. The ORR and corresponding 95%CI will be summarized using F-distribution by binomial probabilities. The difference in ORR between intervention arms will be compared by the stratified Cochran-Mantel-Haenszel (CMH) test. Stratification factors as items specified in section 4.3.

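### Secondary and safety results may be called statistically significant at an unadjusted two-sided 0.05, outside the fixed sequence, even when the gated test of the same comparison fails

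*Protocol*

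**What the plan says.** Protocol 13.2.2 (1) orders five tests: PFS and OS for arm 1 against control, PFS for arm 2 against control, OS for arm 1 against arm 2, and OS for arm 2 against control. The overall level is two-sided 0.05, and "Familywise error rate (FWER) will be controlled by the fixed order test when each hypothesis presupposes the rejection of all previous tests".

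The closing paragraph of 13.2.2 covers everything else. A two-sided test at 0.05 "will be used for secondary efficacy endpoints and safety analysis. Two-sided" P ≤ 0.05 "will be considered statistically significant with a 95%CI". The legend of Figure S4 in the supplementary results carries the same rule. Neither place attaches an order, an alpha split or a condition on the primary results.

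Section 3.6 lists the secondary efficacy endpoints: "PFS per RECIST version 1.1 and iRECIST, ORR, DCR, DOR, 6-month PFS rate, 12-month PFS rate, 12-month OS rate, 18-month OS rate, and QOL". Section 2 plans to compare the secondary measures, ending with "quality of life (QOL) across the three treatment arms". Section 13.4.2 plans between-arm tests for ORR, DCR, DOR, the four landmark rates and the HRQOL items; for example, "The difference in ORR between intervention arms will be compared by the stratified Cochran-Mantel-Haenszel (CMH) test". Section 13.5.2 adds Fisher tests on adverse-event incidence where needed. Section 13.1 mentions key secondary variables but does not name or order them.

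HRQOL is a secondary measure in sections 2 and 3.6, but section 11 says "The exploratory objective of this trial is to evaluate the HRQOL".

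**The concern.** The protocol does more than leave secondary multiplicity open. It states a decision rule that turns any secondary or safety P ≤ 0.05 into a statistically significant result, and that rule lies outside the stated overall 0.05.

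The overlap with the gated hypotheses matters most. The 12- and 18-month OS rates address the same survival comparisons as OS1, OS3 and OS2, and investigator PFS addresses the same comparisons as PFS1 and PFS2. If OS1 misses its boundary, PFS2, OS3 and OS2 are not tested. The landmark OS rates and investigator PFS for those comparisons can still be reported as significant. The reader would then see a significance claim on a question that the sequence had closed.

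**Working it through.** **Plan's own figures.** The protocol gives no family-wise figure for the secondary endpoints, so there is none to reproduce. The nearest stated figures are the OS levels, one-sided 0.0074 and 0.0228.
- Information fraction: 348/497 = 0.70.
- O'Brien-Fleming-type spending at one-sided 0.025: 2 × [1 − Φ(2.2414/√0.70)] = 0.00738, which agrees with 0.0074.
- The pair 0.0074/0.0228 spends 0.0250 in total. The primary OS control is as stated.

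**Number of endpoints (section 3.6).** Investigator PFS by RECIST 1.1 and by iRECIST (2), ORR, DCR, DOR (3), and four landmark rates (4) make 9, or 10 if QOL counts as one test.

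**Number of comparisons.** This is not fixed. Three pairs are possible with three arms; Tables S1 and S2 print P values for two, each active arm against EC alone.

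**Independent endpoints, one comparison.**
- Either direction: 1 − 0.95^9 = 37.0%; 1 − 0.95^10 = 40.1%.
- Favouring arm 1 only: 1 − 0.975^9 = 20.4%; 1 − 0.975^10 = 22.4%.

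**Correlated endpoints.** Simulation under the global null with 1:1:1 allocation, equal correlation ρ between endpoints (assumed; the documents give none), the shared arm built in, and rejection at |Z| > 1.96. Chance of at least one false claim, in per cent, for 9 / 10 endpoints:

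| ρ | one comparison | both active arms vs control | all three pairs | favouring arm 1 vs control |
|---|---|---|---|---|
| 0 | 37 / 40 | 58 / 61 | 69 / 73 | 20 / 22 |
| 0.3 | 33 / 35 | 52 / 55 | 63 / 66 | 16 / 18 |
| 0.5 | 27 / 29 | 44 / 46 | 54 / 56 | 13 / 14 |
| 0.7 | 20 / 21 | 34 / 36 | 42 / 44 | 10 / 11 |
| 0.9 | 12 / 13 | 21 / 22 | 27 / 28 | 6 / 6 |

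The first three columns count rejections in either direction. HRQOL items by visit and the adverse-event tests are not included.

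**Overlap on OS.** Inputs from the protocol: 738/3 = 246 per arm, control median 10 months, 12-month accrual and 18-month follow-up (30-month cut-off), and Fisher's exact test for the landmark rates (13.4.2). Assumptions: exponential survival, no true difference, no dropout, and one unstratified log-rank test at one-sided 0.025.
- Log-rank alone favours the active arm in about 2.5% of trials.
- Log-rank or either landmark rate favours it in about 4.3%.
- A landmark rate is the only favourable OS result in about 1.7%.

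If Fisher's test is replaced by a z-test at 1.96, the last two become about 5.1% and 2.4%. Those are too high for the planned analysis, because Fisher's test is conservative.

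**The case against.** The strongest reply has four parts.

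1. A secondary hierarchy is commonly left to the SAP, which is not at hand, and the sequence figure is not shown. Fair: a missing hierarchy would be no finding. The protocol, however, prints a positive rule for significance, and that rule can be judged as written. Section 13.2.3 does say that later tests stop after a failure, but within the list of primary hypotheses, so it does not clearly gate the secondary tests.

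2. The paragraph sets a threshold. It declares nothing significant in advance, and nothing says that a secondary result may replace a blocked primary test. Correct. A reader might infer that the plan authorises such a substitution, or that the primary family-wise error is inflated; the documents support neither. What stands is that the wording does not prevent a significance claim on the same comparison.

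3. A reader might fix on single figures such as 27% for one comparison or 54% for three. Those need exactly 9 endpoints, correlation 0.5, the global null and, for the second, three pairs that the protocol never specifies. Several endpoints overlap heavily, which points to the lower part of the range, and only about half of the one-comparison figure favours arm 1. Only ranges are defensible.

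4. It would be wrong to say that no secondary measure carries an exploratory label, since section 11 gives HRQOL one. That leaves a conflict of labels to settle.

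**Conclusion.** The point holds as an inexpensive improvement. Section 13.2.2 and the Figure S4 legend let secondary efficacy and safety comparisons be called statistically significant at an unadjusted two-sided 0.05, whatever the outcome of the fixed sequence. Under the assumptions above, the chance of at least one false secondary claim exceeds 5% throughout:
- about 12–40% for one comparison;
- about 21–61% for both active arms against control;
- about 27–73% if all three pairs are tested;
- about 6–22% for a false claim favouring arm 1 over control.

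For OS alone the excess is modest: about 4.3% against 2.5%, with 1.7% from landmark rates only. Error control over the five primary hypotheses is intact.

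**What to change.** Replace the closing paragraph of 13.2.2, and the matching sentences in the Figure S4 legend, with wording to this effect:

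> Secondary efficacy endpoints, HRQOL and safety comparisons lie outside the family-wise error control. They are reported with estimates, 95% confidence intervals and nominal P values, and support no claim of statistical significance.

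If the sponsor wants a secondary claim, name the endpoint and the comparison and append that test to the end of the existing fixed sequence. It would then be tested only after OS2 has succeeded, and the overall 0.05 would hold.

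Give HRQOL one label across sections 2, 3.6 and 11.

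The cost is wording only: data, sample size and primary tests do not change. The downside is that the sponsor gives up unadjusted significance claims for secondary endpoints.

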### 13.2.3 Hypothesis

The primary efficacy endpoints of this trial are PFS and OS.

Comparison between groups will be performed using a stratified log-rank test:

➤ PFS hypothesis 1 (Intervention arm 1 vs. Control arm)

$H_{0(PFS1)}$ : PFS in intervention arm 1 = PFS in the control arm, that is,  $S_1(t) = S_2(t)$ ;

$H_{1(PFS1)}$ : PFS in intervention arm 1  $\neq$  PFS in the control arm, that is,  $S_1(t) \neq S_2(t)$ ;

*If the test for PFS does not reject the null hypothesis  $H_{0(PFS1)}$ , all subsequent tests will be terminated; if  $H_{0(PFS2)}$  is rejected, tests will be continued. This result will demonstrate the superiority of PFS in intervention arm 1 compared with the control arm.*

➤ OS hypothesis 1 (Intervention arm 1 vs. Control arm)

$H_{0(OS1)}$ : OS in intervention arm 1 = OS in the control arm, that is,  $S_1(t) = S_2(t)$ ;

$H_{1(OS1)}$ : OS in intervention arm 1  $\neq$  OS in the control arm, that is,  $S_1(t) \neq S_2(t)$ ;

*If the test for OS does not reject the null hypothesis  $H_{0(OS1)}$ , all subsequent tests will be terminated; if  $H_{0(OS1)}$  is rejected, tests will be continued.*

➤ PFS hypothesis 2 (Intervention arm 2 vs. Control arm)

$H_{0(PFS2)}$ : PFS in intervention arm 2 = PFS in the control arm, that is,  $S_1(t) = S_2(t)$ ;

$H_{1(PFS2)}$ : PFS in intervention arm 2  $\neq$  PFS in the control arm, that is,  $S_1(t) \neq S_2(t)$ ;

*If the test for PFS does not reject the null hypothesis  $H_{0(PFS2)}$ , all subsequent tests will be terminated; if  $H_{0(PFS2)}$  is rejected, tests will be continued.*

➤ OS hypothesis 3 (Intervention arm 1 vs. Intervention arm 2)

$H_{0(OS3)}$ : OS in intervention arm 1 = OS in the control arm, that is,  $S_1(t) = S_2(t)$ ;

$H_{1(OS3)}$ : OS in intervention arm 1  $\neq$  OS in the control arm, that is,  $S_1(t) \neq S_2(t)$ ;

*If the test for OS does not reject the null hypothesis  $H_{0(OS3)}$ , all subsequent tests will be terminated; if  $H_{0(OS3)}$  is rejected, tests will be continued.*

➤ OS hypothesis 2 (Intervention arm 2 vs. Control arm)

$H_{0(OS2)}$ : OS in intervention arm 2 = OS in the control arm, that is,  $S_1(t) = S_2(t)$ ;

$H_{1(OS2)}$ : OS in intervention arm 2  $\neq$  OS in the control arm, that is,  $S_1(t) \neq S_2(t)$ ;

### 13.3 Study Population

#### 13.3.1 Subject Disposition

Subject disposition (analysis of population allocation, enrollment at each center, loss to follow-up, treatment period, and treatment discontinuation) will be summarized using frequency and percentage.

Subject allocation and reasons for analysis exclusion in each analysis set will be summarized.

Listings will be provided for subjects who are excluded for analysis (specific protocol deviations and reasons for exclusion).

A by-subject listing will be provided to describe the treatment and reasons for treatment discontinuation.

#### 13.3.2 Protocol Deviation

A by-subject listing of subjects with protocol deviations will be provided by the intervention arm in the ITT population.

#### 13.3.3 Demographics and Baseline Characteristics

Age will be summarized by mean, SD, minimum, maximum, and median.

Gender will be summarized by frequency counts.

Height and weight will be summarized by mean, SD, minimum, maximum, and median.

Tumor history, including TNM stage, history of antitumor therapy, and smoking history, will be summarized by frequency counts.

Baseline vital signs (temperature, heart rate, breathing, and blood pressure): baseline is defined as the latest non-missing assessment before the first dose.

Baseline ECOG PS will be summarized by mean, SD, minimum, maximum, and median.

### **13.4 Efficacy Analysis**

#### **13.4.1 Analysis of Primary Efficacy Endpoints**

##### **➤ PFS**

The median PFS will be estimated using the Kaplan-Meier method and presented with the Kaplan-Meier curve.

The comparison of PFS between intervention arms will be performed using a stratified log-rank test. The HR and the corresponding 95%CI will also be provided based on a Cox proportional hazard model, using ECOG PS (0 vs. 1), brain metastases (yes vs. no), and liver metastases (yes vs. no) as concomitant variables. The results of the unstratified log-rank test and results of the Cox proportional hazard model without covariates adjustment will also be provided.

Subgroup analysis of PFS will be performed based on stratification factors.

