#### (2) Type I error control for the re-estimation of sample size based on PFS

The safety analysis, re-estimation of sample size, and efficacy analysis will be conducted by the iDMC. The re-estimation of sample size based on PFS is planned after 50% of the planned PFS events (174 cases). At the same time, a safety analysis will be performed. The interim analysis will be conducted by iDMC.

The non-blind re-estimation of sample size is a procedure with multiple tests, with a concern on data dependency in different stages, which would increase the inflation of the type I error rate. To address this problem, P values in two stages will be combined using the MSP.

According to the preliminary test, in the PFS interim analysis based on the re-estimation of sample size, the one-side significance level is set as  $\alpha_1=0.005$ , and the futility boundary is set as  $b_1=0.45$  in the first stage; the one-side significance level is set as  $\alpha_2=0.2050$  in the secondary stage. No early discontinuation of the study due to PFS efficacy would be considered.

- Either  $P_1 \leq \alpha_1$  or  $P_1 > \alpha_1$ , once  $P_1 \leq b_1$ , the trial will continue to the second stage, without early discontinuation due to PFS efficacy;

- If  $P_1 > b_1$ , the trial will terminate early for futility;
- If the trial could proceed into the second stage,  $P_1 + P_2 \leq \alpha_2$  [that is, adjust P value =  $\alpha_1 + (P_1 + P_2)(b_1 - \alpha_1) - 1/2 (b_1^2 - \alpha_1^2) \leq 0.025$ ], the between-group difference in PFS will be considered as statistically significant.

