##### **➤ OS**

The median OS will be estimated using the Kaplan-Meier method and presented with the Kaplan-Meier curve.

The comparison of OS between intervention arms will be performed using a stratified log-rank test. The HR and the corresponding 95%CI will also be provided based on a Cox proportional hazard model, using ECOG PS (0 vs. 1), brain metastases (yes vs. no), liver metastases (yes vs. no), and treatment after patient withdrawal (yes vs. no) as concomitant variables. The results of the unstratified log-rank test and results of the Cox proportional hazard model without covariates adjustment will also be provided.

Subgroup analysis of OS will be performed based on stratification factors.

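### The reported hazard ratios do not come from the model behind the stratified log-rank test; for OS the Cox model also adjusts for treatment after withdrawal, a post-randomisation variable

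*Protocol*

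**What the plan says.** **The test.** Section 13.2.3 states: "Comparison between groups will be performed using a stratified log-rank test". Section 13.4.1 repeats this for each endpoint: "The comparison of PFS between intervention arms will be performed using a stratified log-rank test" and "The comparison of OS between intervention arms will be performed using a stratified log-rank test". Section 4.3 gives the randomisation strata: ECOG PS, brain metastases and liver metastases.

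**The estimate.** For PFS, section 13.4.1 provides the HR and 95% CI "based on a Cox proportional hazard model, using ECOG PS (0 vs. 1), brain metastases (yes vs. no), and liver metastases" as concomitant variables. For OS it says "The HR and the corresponding 95%CI will also be provided based on a Cox proportional hazard model", and the covariate list has a fourth item, whether the patient had treatment after withdrawal (yes or no). For both endpoints an unstratified log-rank test is added, and "results of the Cox proportional hazard model without covariates adjustment will also be provided". No stratified Cox model is named.

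**The decision levels.** Section 13.2.2 (2) stops for futility if P1 exceeds 0.45. Otherwise, if P1 + P2 is at most 0.2050, "the between-group difference in PFS will be considered as statistically significant". Section 13.2.2 (3) sets one-sided levels of 0.0074 at the OS interim and 0.0228 at the OS final. The CI is 95% throughout, and the protocol does not say how to read it when it and the decision rule differ.

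**The concern.** The HR and its interval are how the size of the benefit will be read, so they should estimate what the deciding test examines. There are two departures, of unequal weight.

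1. **Model.** Entering the three baseline factors as covariates imposes one baseline hazard shape and additive log-hazard effects, which the stratified test does not assume. That is a modest difference. The fourth OS covariate is another matter. Whether a patient receives further treatment depends on progression, toxicity and survival up to that point, all of which the assigned treatment can change. Conditioning on it can remove part of the treatment effect or create a spurious one. Coded as a fixed yes/no, it also gives the yes group guaranteed survival up to the start of that treatment. The no group mixes early deaths with patients still on study drug.

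2. **Level.** At the OS interim a 95% interval is far less demanding than the boundary. Section 4.2 links the timing of that interim to the final PFS analysis, and OS1 is the gate to PFS2, OS3 and OS2 in section 13.2.2 (1). The interim OS result is therefore one that people will want to interpret.

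**Working it through.** **The plan's levels reproduce.** O'Brien-Fleming-type spending at one-sided 0.025 and 70% information gives 0.00738 and 0.02275, against the stated 0.0074 and 0.0228. The sum-of-P rule gives 0.005 + (0.2050 − 0.005)²/2 = 0.025. The decision rules are not in question here.

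**Baseline covariates against strata.** Stratified log-rank and covariate-adjusted Cox were simulated with 246 patients per arm, 232 or 331 events and 800 runs per setting. Assumed, not in the protocol: ECOG 1 in 80%, brain metastases 10%, liver metastases 30%, log-HRs 0.3, 0.3 and 0.5. At true HR 0.70 to 0.80 the z statistics correlate at 0.99, and at equal level the two methods disagree in about 1% to 5% of trials. A second set of assumptions (85/12/33%, including non-proportional stratum hazards) gave 2% to 9%, against 0% to 0.2% for a stratified Cox model. The stratified log-rank is the score test of that stratified model (no ties), which explains the near-complete agreement. None of these runs includes the post-withdrawal covariate.

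**Post-withdrawal covariate in the OS model.** The plan's own assumptions make it depend on arm. Sections 4.1.2 and 4.1.3 give PFS hazards of 0.1733 (control) and 0.1040 (arm 1). Section 4.1.1 gives 12 months' accrual and a control median OS of 10 months. With 738 patients and OS HRs of 0.70 and 0.72, 348 deaths fall at about month 17.85, so follow-up runs from 5.85 to 17.85 months. The share still without a PFS event is [exp(−5.85h) − exp(−17.85h)]/(12h):
- control: (0.363 − 0.045)/2.080 = 0.153, so about 85% have had a PFS event;
- arm 1: (0.544 − 0.156)/1.248 = 0.311, so about 69% have.

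This ignores dropout. The opportunity for further treatment therefore differs by design. An illustrative simulation under assumed subsequent-therapy patterns moved the mean OS HR from 0.69 to 0.66 in one case and from 0.71 to 0.77 in another. The protocol gives no such patterns, so this shows that either direction is possible; it is not a forecast.

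**Level, OS interim.** The two-sided interval matching 0.0074 is 1 − 2 × 0.0074 = 98.52%. Pairwise events are about 348 × 2/3 = 232, or 106 + 135, about 240, under the plan's hazards. With 232 events:
- the boundary needs an observed HR of at most exp(−2 × 2.437/√232) = 0.726;
- a 95% CI excludes 1 from exp(−2 × 1.960/√232) = 0.773 downwards.

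The chance of landing between, with Z ~ N(−ln(HR) × √(d/4), 1), is:

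| True HR | Events d | P(0.0074 < P < 0.025) |
|---|---|---|
| 0.70 | 240 | 16.1% |
| 0.72 | 240 | 17.8% |
| 0.75 | 232 | 18.9% |
| 0.80 | 232 | 16.7% |

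**Level, OS final.** The matching interval is 95.44%. With 331 events the HR thresholds are 0.803 and 0.806, and the chance of landing between is 0.7% to 1.6% at HR 0.70 to 0.80.

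**PFS rule.** Two equal independent stages, futility at 0.45, 2 million draws:

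| True HR | Events | CI excludes 1, rule fails | Rule met, CI includes 1 |
|---|---|---|---|
| 0.60 | 165 | 6.9% | 0.8% |
| 0.60 | 240 | 3.4% | 0.2% |
| 0.65 | 231 | 6.9% | 0.8% |
| 0.75 | 240 | 9.7% | 2.0% |

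The 165 events belong to the stand-alone calculation in section 4.1.2. At the trial's own trigger of 347 PFS events (section 4.1.4), the plan's hazards put about 102 + 138 = 240 in arm 1 plus control.

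**The case against.** The strongest reply is that the document does not contradict itself. Sections 13.2.2 and 13.2.3 decide success by P values alone, and the interval is only additional output. Nominal 95% intervals beside sequential boundaries are ordinary practice, and their labelling is often left to the SAP, which is not shown. For PFS, both methods account for the same three factors. This stands, and it limits the point.

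Four stronger readings are tempting, and the documents do not support them:
- **That an interval could overturn or create a success claim, or that type I error is affected.** No section gives the interval a deciding role.
- **That interim OS intervals will be published beside the PFS result.** Section 4.2 links the timing and assigns the analysis to the iDMC. It says nothing of releasing an uncrossed interim.
- **That PFS needs an interval obtained by inverting the sum-of-P rule.** The overall PFS level is still one-sided 0.025, so the disagreement comes from the combination rule and not from 95% as such. The inversion would need its own pre-specified stage-wise method, and its benefit is debatable.
- **That PFS and OS share one model defect.** They do not: the post-withdrawal covariate is in the OS model only.

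The reply does not cover that covariate. The protocol itself writes it into the model for a primary endpoint. It is not a detail left open for the SAP.

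**Conclusion.** The point holds, at minor to moderate severity. In order of weight:

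1. **OS model: material.** The reported HR conditions on a post-randomisation variable and so does not estimate the effect that the stratified log-rank assesses. That follows from the text alone. The size of the bias cannot be derived from the protocol, and the simulated shifts rest on assumed therapy patterns.
2. **OS interim level: worth fixing.** The 16% to 19% assumes proportional hazards and 232 to 240 pairwise deaths.
3. **PFS rule against 95% CI: a labelling matter.** Disagreement is about 4% at HR 0.60 with 240 events, 8% at HR 0.65 with 231, and 12% at HR 0.75 with 240.
4. **Baseline covariates against strata: small.** The figures depend on assumed prevalences and effects, and were not run on PFS event counts.
5. **OS final level: negligible.**

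**What to change.** In section 13.4.1:
- For PFS and OS, take the primary HR and CI from a Cox model stratified by ECOG PS, brain metastases and liver metastases, with treatment as the only covariate.
- Keep the model adjusted for the three baseline factors and the unadjusted model as supportive.
- Remove treatment after withdrawal from the OS model, or confine it to an analysis labelled exploratory.
- At the OS interim, add a 98.52% interval or state that the 95% CI is descriptive. No change of level is needed at the OS final.
- For PFS, state that significance rests on the two-stage sum-of-P rule and that the 95% CI is descriptive.

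The cost is protocol wording and a small change to the analysis programs. Sample size, conduct and the decision rules are untouched. The 98.52% interval is about 24% wider than the 95% one on the log-HR scale (2.437/1.960 = 1.24); labelling the 95% interval descriptive avoids that.
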